### Inclusion/exclusion criteria

Women will be eligible for inclusion into this trial if they are expected to deliver vaginally, have a cervical dilatation equal to or less than 6 cm, have a known singleton pregnancy and have provide written informed consent. Women will not be eligible for study participation if they: 1) are in an advanced first stage of labour (>6 cm cervical dilatation) or are too distressed to understand, confirm and give informed consent regardless of cervical dilatation; 2) are non-emancipated minors (as per local regulations) without a guardian; 3) have been scheduled for a planned caesarean section; 4) have a birth considered to be an abortion according to local guidelines; 5) have known allergies to carbetocin, other oxytocin homologues or excipients in the medicinal products used in the trial; 6) have serious cardiovascular disorders; 7) have serious hepatic or renal disease; 8) have epilepsy; or 9) are not capable of giving consent due to other health problems such as obstetric emergencies (for example, antepartum haemorrhage) or mental disorder.

Participants will be free to discontinue the trial at any time without giving their reason(s). Participants who withdraw will not be replaced; that is, randomized numbers will be uniquely linked to each participant. Data collected up to that point will be included unless participants request the opposite. After a participant has completed the trial or has withdrawn early, usual treatment will be administered, if required, in accordance with the trial centre’s standard of care and generally accepted medical practice and depending on the participant’s individual medical needs.

### Randomization

The random allocation sequence will be generated centrally at WHO headquarters using computer-generated random numbers. Randomization will be stratified by country and will use permuted blocks, with an allocation ratio of 1:1. Participants will randomly be assigned within each country to one of the two treatment groups: oxytocin 10 IU IM or carbetocin RTS 100 μg IM. Allocation of the randomly generated sequence will be performed by consecutively numbered treatment packs arranged in dispensers.

### Primary and secondary endpoints

The primary and secondary endpoints are listed in Table 2. The trial is being conducted as an effectiveness trial with the objective of carbetocin RTS being registered for the indication “prevention of postpartum haemorrhage” by drug regulatory authorities if it is shown to be non-inferior or superior to oxytocin. The primary composite endpoint is blood loss ≥500 mL or use of additional uterotonics. For the purpose of evaluating clinical effectiveness and for the potential inclusion of carbetocin RTS in future WHO guidelines and the Model List of Essential Medicines, the more substantive endpoint of blood loss ≥1,000 mL is also a primary endpoint. Since the two primary endpoints serve independent objectives, there will be no adjustment for the type I error rate for multiplicity of endpoints.

**Table 2 Tab2:** Primary and secondary endpoints

Primary endpoints
The proportion of women: • with blood loss of 500 mL or more or the use of additional uterotonics at one hour and up to two hours for women who continue to bleed after one hour; • with blood loss of 1,000 mL or more at one hour and up to two hours for women who continue to bleed after one hour.
Secondary endpoints
The proportion of women: • with blood loss of 500 mL or more at one hour (or two hours postpartum if the bleeding continues beyond one hour); • receiving additional uterotonics at one hour (or two hours postpartum if the bleeding continues beyond one hour); • receiving additional uterotonics up to time of discharge; • receiving blood transfusion up to time of discharge; • with manual removal of placenta up to time of discharge; • having additional surgical procedures (for example, suturing of cervix/high vaginal tear, exploration of uterine cavity under general anaesthetic, uterine compression suture, uterine or hypogastric ligation, hysterectomy) up to time of discharge; • with maternal death; • with composite outcome of maternal death or severe morbidity (admission to intensive care unit, hysterectomy, blood loss of two litres or more, uterine inversion) up to time of discharge Blood loss in mL at one hour (or two hours postpartum if the bleeding continues beyond one hour). The incidence and severity of adverse or serious adverse events up to the time of discharge. Newborn outcomes (vital status, Apgar score at 5 minutes, resuscitation of the baby, mechanical ventilation).

### Assessment of efficacy

Efficacy will be assessed using blood loss volume measurement per the two primary endpoints listed in Table 2. Blood loss will be measured using a calibrated drape [12], which will be placed under the participant’s buttocks once the cord is clamped (1–3 minutes after delivery of the baby) and cut. Blood loss will be measured for one hour, or for two hours postpartum, if the bleeding continues beyond one hour. Blood loss weight in grams will be converted to millilitres by dividing the figure in grams by 1.06 (blood density in grams per millilitre) [13].

### Assessment of safety

Comprehensive assessment of the safety of the study drugs will be performed throughout the course of the trial, from the time of the participant’s signature of informed consent until discharge. Trial centre personnel will report any adverse event (AE), whether observed by the investigator or reported by the participant.

The intensity of an AE will be classified using a three-point scale: mild ─ awareness of signs or symptoms, but no disruption of usual activity; moderate ─ event sufficient to affect usual activity; and severe ─ inability to work or perform usual activities. AEs will also be classified as possibly related to study drug (that is, there is evidence or argument to suggest a causal relationship between the AE and the study drug), or not related to study drug (that is, there is no reasonable evidence or argument to suggest a causal relationship between the AE and the study drug).

The outcome of an AE will be classified as: recovered/resolved (fully recovered or the condition has returned to the level observed at initiation of trial treatment); recovered/resolved with sequelae (resulted in persistent or significant disability/incapacity); recovering/resolving; not recovered/not resolved; or fatal.

An AE will be considered serious if it results in death, is life-threatening, requires in-patient hospitalization or prolongation of existing hospitalization, results in persistent or significant disability/incapacity, is a congenital anomaly/birth defect, or is an important medical event. If an investigator becomes aware of a serious AE after the participant’s hospital discharge, and he/she assesses the serious AE to have a reasonable possible causality to the study drug, the case will be reported, regardless of how long after the end of the trial the AE took place.

Since the amount of blood lost is collected as an efficacy endpoint, only the following blood loss events that fulfil the criteria for a serious AE will be recorded: ICU admission (adult ICU admission, not maternity/labour ward high care); surgical intervention for control of haemorrhage (hypogastric artery ligation or uterine compression sutures); peripartum hysterectomy, blood loss ≥ 2,000 mL; and uterine inversion.

### Sample size calculation

The two endpoints that guided the sample size estimation for the trial were sPPH (blood loss ≥1,000 mL), PPH (blood loss ≥500 mL) or the use of additional uterotonics. Severe PPH is a more serious endpoint that is closely associated to severe maternal morbidity and related to additional interventions. The sPPH endpoint is also less frequent and thus guided the overall sample size estimation.

A non-inferiority design was chosen since the aim of the trial is to determine if carbetocin RTS is non-inferior in efficacy to the standard intervention (oxytocin 10 IU IM). In order to demonstrate non-inferiority within a margin of 0.46 %, with a power of 80 % and with a significance level of 2.5 %, a total of 29,082 women are needed assuming an equal sPPH prevalence of 2 % with both treatments, calculated by the standard formula (see Additional file 2 for the rationale of the choice of the margin) [14]. The margin of 0.46 % on the difference scale corresponds to 1.23 on the relative scale for the assumed prevalence. Figure 1 shows the total sample size required to assess non-inferiority at the 2.5 % level of significance (usually required for non-inferiority trials) for different scenarios. We also assumed, from a similar large trial [15], a 3 % loss of study participants who are eligible to contribute to the analysis due to exclusion of women with a caesarean section or abortion after randomization, and those who are not protocol-compliant (excluded only in the per-protocol analysis), bringing the sample size to 30,000. This sample size will provide 90 % power for a conventional two-sided 5 % test of superiority to detect a minimum significant difference between 1.5 % and 2 % in the rate of sPPH for the two treatment groups.

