**Fig. 1 Fig1:**
[figure not shown]
Total sample size for non-inferiority with equal proportions = 1.5 % or 2 %, 80 % power and different values of the margin on the relative scale

Similarly, we calculated the sample size for the composite endpoint defined as blood loss ≥500 mL or administration of additional uterotonics. With active management, the risk of this event is estimated as 16 % (personal communication) [15]. Assuming equal prevalence for this event of 16 % with both treatments, in order to demonstrate non-inferiority within a margin of 1.16 on the relative scale, with a power of 80 % and with a significance level of 2.5 %, a total of 6,242 women are needed. With 30,000 women the power obtained would be more than 99 % [14]. This sample size will provide a power of 99.5 % for a conventional two-sided 5 % test of superiority to detect a minimum significant difference between 16 % and 18 % in the occurrence of PPH or administration of additional uterotonics for the two treatment groups (Stata version 13.1).

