### Statistics

Safety and tolerability will be assessed by a review of AEs, by conducting inferential testing with significance levels for between-group comparisons. The between-treatment difference for the occurrence of AEs will be tested using the stratified Mantel-Haenszel chi-square if frequencies are sufficiently high, or otherwise with exact methods taking stratification into account.

For efficacy, non-inferiority will be assessed using a two-sided 95 % confidence interval (CI) for the relative risk (RR) of sPPH and of PPH or additional uterotonic use (carbetocin RTS versus oxytocin). The upper limit of the two-sided 95 % CI for the RR for the composite endpoint of blood loss ≥500 mL or additional uterotonic use will be compared to the non-inferiority margin of 1.16. The upper limit of the two-sided 95 % CI for the RR for the endpoint of blood loss ≥1,000 mL will be compared to the non-inferiority margin of 1.23. If the upper limit is below the corresponding margin, non-inferiority will have been demonstrated. This upper limit is the same as the upper limit of the one-sided 97.5 % CI; therefore, the significance level for the non-inferiority test will be 2.5 % (one-sided). For each endpoint, to declare carbetocin RTS non-inferior to oxytocin, we will require non-inferiority to be demonstrated for both PP and the modified ITT analyses. If non-inferiority is demonstrated, a two-tailed superiority test will be conducted at 5 % level of significance. Interpretation will be as in Fig. 1 of Piaggio et al. [16]. Comparisons will also be expressed as risk differences with 95 % CIs.

The statistical technique used to conduct tests and obtain CIs for the main endpoints will be a logistic model with a binary endpoint, a binomial distribution and the log link to obtain RRs. The identity link will be used to obtain risk differences. Stratifying variables (country) will be included in the model. The model will be fitted using SAS Software version 9.3 (SAS Institute Inc., Cary, NC, USA). A separate model will be fitted for each of the two primary endpoints.

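### The 80% power for severe PPH was calculated for a fixed risk-difference margin; under the declared relative-risk rule the same sample gives about 71%

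*Protocol article*

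**What the plan says.** The Sample size calculation section plans severe PPH on the difference scale. It begins "In order to demonstrate non-inferiority within a margin of 0.46" percentage points, with 80% power and a 2.5% significance level, and concludes that "a total of 29,082 women are needed assuming an equal sPPH prevalence of" 2% with both treatments. It links this to the relative scale by saying that the margin "corresponds to 1.23 on the relative scale for the assumed prevalence". A 3% loss then takes the total to 30,000. The same section says that severe PPH, as the rarer endpoint, determined the overall size.

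The Statistics section decides on another scale. There, the upper 95% confidence limit of the relative risk of severe PPH "will be compared to the non-inferiority margin of 1.23". The model has "a binomial distribution and the log link to obtain RRs", with country included, and "the significance level for the non-inferiority test will be 2.5"% one-sided. Non-inferiority must be shown in both the per-protocol and the modified ITT populations. Risk differences with 95% CIs are reported as well, but no decision is attached to them. The Abstract and the section on primary objectives and hypotheses also state the margin as a relative risk of 1.23.

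The caption of Fig. 1 describes total sample size at prevalences of 1.5% and 2% for "different values of the margin on the relative scale".

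**The concern.** The stated power belongs to a test that the trial will not use for its decision. A margin of 0.46 points and a relative risk of 1.23 mark the same point when the control rate is exactly 2%, but that does not make the two confidence-interval rules equally likely to succeed. If the relative-risk rule has lower power, the chance of missing non-inferiority when the drugs are truly equal is larger than the 20% that a reader would take from the article.

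The stakes are practical. According to the section on primary and secondary endpoints, severe PPH is the endpoint meant to inform WHO guidelines and the essential medicines list. Superiority is tested only after non-inferiority has been shown. An inconclusive result on this endpoint would be interpreted against a power that the design does not have.

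**Working it through.** **Inputs.** From Sample size calculation: p = 0.02 in both arms, difference margin 0.0046, power 80%, one-sided 2.5%, 30,000 women with 3% loss, so 30,000 × 0.97 = 29,100 evaluable. From Statistics: relative-risk margin 1.23 and log link. From Randomization: 1:1 allocation. The calculation uses the plan's single 2% rate and ignores country, because the article gives no rates by country.

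**1. Reproduce the plan's figure (difference scale).**

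n per arm = 2p(1−p)(1.960 + 0.8416)² / 0.0046² = 2 × 0.02 × 0.98 × 7.849 / 0.00002116 = 14,540.5, rounded up to 14,541. The total is 29,082, an exact match, with power 80.0%. Also, 29,082 / 0.97 = 29,981, which supports 30,000.

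**2. Power under the declared rule (log relative risk), n = 14,541 per arm.**

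- SE(log RR) = √[2(1−p)/(np)] = √[2 × 0.98 / (14,541 × 0.02)] = 0.0821
- ln(1.23) = 0.2070
- Power = Φ(0.2070/0.0821 − 1.960) = Φ(0.562) = 71.3%

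**3. Where the loss comes from.** On the difference scale the SE is √(2 × 0.02 × 0.98 / 14,541) = 0.001642. Dividing SE and margin by 0.02 gives an SE of 0.0821 and a margin of 0.23. The standardised SE is therefore identical, and only the distance to the margin changes:

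| Rule | Distance | SE | Ratio | Power |
|---|---|---|---|---|
| Difference, 0.46 points (÷ 0.02) | 0.230 | 0.0821 | 2.80 | 80.0% |
| Log relative risk, 1.23 | 0.207 | 0.0821 | 2.52 | 71.3% |

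**4. Simulation.** With 1,000,000 trials at 29,082 women and 2% in both arms, the log-RR interval met its criterion in 71.2%, a Farrington-Manning score test of RR = 1.23 in 71.3%, and the difference interval against 0.46 points in 80.0%. The shortfall is therefore not an artefact of the Wald interval.

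**5. Other sample sizes and rates (relative-risk rule).**

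- 29,100 evaluable: 71.3%. All 30,000 evaluable: 72.6%.
- At 29,082 with other common rates: 58.6% at 1.5%, 66.6% at 1.8%, 80.7% at 2.5%.

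**6. What 80% would take.**

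- Sample: 7.849 × 2 × 0.98 / (0.02 × 0.2070²) ≈ 17,949 per arm, or about 35,900 evaluable (about 37,000 randomized with 3% loss).
- Margin at the planned size: exp(2.80 × 0.0821) = exp(0.230) ≈ 1.26.

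**7. Composite endpoint.** At 16% in both arms and margin 1.16, the relative-risk rule needs about 7,480 women. Its power exceeds 99.9% at both 29,100 and 30,000, so the article's claim of more than 99% stands.

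**The case against.** The best defence is that nothing is miscalculated. The article says openly that the 0.46-point margin is on the difference scale, limits the equivalence with 1.23 to the assumed prevalence, and attaches the 80% to the 0.46-point margin, for which it is correct. All of that stands. It does not settle the matter, because no decision in the article uses the 0.46-point margin.

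A second defence is that power is a planning quantity. Type I error, bias and the reading of the observed interval against 1.23 do not depend on it. This also stands, and it limits the point to a misstated power.

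Third, 71% is specific to exact equality. At a true relative risk of 0.97 the same rule has about 82% power, and at 0.95 about 87%. But equality is the plan's own assumption, and the stated 80% rests on it.

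Fourth, non-compliant women leave only the per-protocol set, so the modified ITT set may exceed 29,100. Its power then lies between 71.3% and 72.6%.

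A reader might go further in three ways that the document does not support:

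- That the relative-risk test loses power through a larger variance. In the log-link form that the plan specifies, the standardised SE is the same; the loss comes from the logarithm of the margin.
- That Fig. 1 is wrong. Its caption gives margins on the relative scale, but the curves are not in the text at hand and the formula behind them cannot be confirmed.
- That the requirement for both populations costs a definite further amount. It cannot raise power, but the article does not give the overlap needed to say how much it lowers it.

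**Conclusion.** The point holds as a mismatch between the scale used for planning and the scale used for the decision. With 2% severe PPH in both arms, one-sided 2.5% and a relative-risk margin of 1.23, the power is about 71% at 29,082 to 29,100 evaluable women and at most 72.6% if none of the 30,000 is lost. The chance of failing to show non-inferiority when the drugs are equal is therefore about 29%, not 20%, and the requirement for both populations cannot reduce it.

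This does not show that the sample size was computed wrongly from its stated inputs, that the decision rule is invalid, or that more women must be enrolled. Neither type I error nor the composite endpoint is materially affected. The size of the shortfall rests on the plan's assumed 2% rate and true equality.

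**What to change.** Keep the 30,000 women, the 1.23 margin and the decision rule. In the Sample size calculation section, restate the severe-PPH non-inferiority power as about 71%, and give its conditions: 2% in both arms, relative-risk margin 1.23, one-sided 2.5%, about 29,100 evaluable women. Compute it with ln(margin) as the distance and 2(1−p)/(np) as the variance of the log relative risk. Both parts are needed: that variance paired with a linear margin of 0.23 simply returns 80%.

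The 29,082 can stay as the historical basis if it is labelled as a difference-scale calculation. If Fig. 1 was drawn with the difference formula, recompute it in the same way; if it already uses the log relative risk, leave it and say so.

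The cost is one reworded paragraph, possibly one redrawn figure, and a less favourable stated power. The Trial status section reports recruitment under way in only five of the ten countries, so the correction can be made before results are known.

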**Fig. 1 Fig1:**
[figure not shown]
Total sample size for non-inferiority with equal proportions = 1.5 % or 2 %, 80 % power and different values of the margin on the relative scale

Similarly, we calculated the sample size for the composite endpoint defined as blood loss ≥500 mL or administration of additional uterotonics. With active management, the risk of this event is estimated as 16 % (personal communication) [15]. Assuming equal prevalence for this event of 16 % with both treatments, in order to demonstrate non-inferiority within a margin of 1.16 on the relative scale, with a power of 80 % and with a significance level of 2.5 %, a total of 6,242 women are needed. With 30,000 women the power obtained would be more than 99 % [14]. This sample size will provide a power of 99.5 % for a conventional two-sided 5 % test of superiority to detect a minimum significant difference between 16 % and 18 % in the occurrence of PPH or administration of additional uterotonics for the two treatment groups (Stata version 13.1).

### Analysis populations

Analyses will be performed in three populations: intention-to-treat (ITT), modified ITT, and per-protocol. The ITT population includes all randomized participants, using the treatment as randomized. The modified ITT analysis excludes women having a caesarean section after randomization and those withdrawing consent. The per-protocol population includes all participants randomized into the trial, who were compliant with, and treated according to, the protocol, and who fulfil the following criteria: compliance with all entry criteria, absence of major clinical trial protocol violations with respect to factors likely to affect the efficacy of treatment, and adequate compliance with trial medication (giving oxytocin or carbetocin to women as randomized). Declaring carbetocin RTS non-inferior to oxytocin will require non-inferiority to be demonstrated for both per-protocol and the modified ITT analyses. For testing the superiority of each endpoint, the modified ITT analysis will be the main analysis. The primary population for safety analysis will consist of all women receiving treatment.

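### The modified ITT set drops every woman who withdraws consent, although the protocol keeps data collected before withdrawal; the effect is probably small, and one clause settles it.

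*Protocol article*

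**What the plan says.** Two statements in the protocol article bear on women who withdraw.

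- Inclusion/exclusion criteria, after stating that participants may leave the trial at any time: "Data collected up to that point will be included unless participants request the opposite".
- Analysis populations: "The modified ITT analysis excludes women having a caesarean section after randomization and those withdrawing consent". This carries no exception for women who leave their data available.

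The modified ITT set carries the main decisions. For non-inferiority: "Declaring carbetocin RTS non-inferior to oxytocin will require non-inferiority to be demonstrated for both per-protocol and the modified ITT analyses". For superiority: "For testing the superiority of each endpoint, the modified ITT analysis will be the main analysis". The Statistics section also uses it for the secondary binary endpoints. The full ITT set keeps everyone ("The ITT population includes all randomized participants, using the treatment as randomized"), but no primary decision rests on it.

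The Sample size calculation section assumes "a 3 % loss of study participants who are eligible to contribute to the analysis". It attributes this loss to "exclusion of women with a caesarean section or abortion after randomization" and to non-compliers, who are removed from per-protocol only. It names abortion, which the modified ITT definition does not, and it does not name withdrawal of consent.

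**The concern.** A woman who withdraws but does not refuse use of her data is kept by one rule and, on a literal reading, removed from the decisive set by the other.

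The two modified ITT exclusions differ in kind. The study drug is given after the baby is born, so a caesarean section after randomisation comes before dosing and, under blinding, cannot depend on the drug. Withdrawal of consent can come at any time up to discharge or transfer, whereas the primary endpoints are complete one to two hours after birth. A woman can therefore withdraw once her primary outcome is known, perhaps because of bleeding, an adverse event or an intervention. Removing her discards an observed primary outcome on the basis of something that happened after treatment. If the drugs differ in those respects, the loss need not be equal between arms.

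**Working it through.** **Time order (Study design; Table 2).** Randomisation when vaginal delivery is imminent; birth; injection; blood loss measured for one hour, or two if bleeding continues; end of participation at discharge or transfer. Withdrawal after measurement is therefore possible.

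**The plan's own figure.** Inputs from Sample size calculation: severe PPH 2 % in both arms, margin 0.46 percentage points, one-sided 2.5 %, power 80 %.

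- n per arm = (1.960 + 0.842)² × 2 × 0.02 × 0.98 / 0.0046² = 14,541 with unrounded normal quantiles, so 29,082 in total. This matches the plan.
- 29,082 / 0.97 = 29,982, rounded to 30,000. This also matches.

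**Expected events.** 30,000 × 0.97 = 29,100; at 1:1 allocation, 14,550 per arm; × 0.02 = 291 severe PPH events per arm.

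**Upper limit.** The Statistics section compares the upper limit of the two-sided 95 % interval for the relative risk with 1.23, so the limit matters and not only the point estimate. I used the log relative-risk interval, unadjusted for country:

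SE = √(1/a − 1/n₁ + 1/b − 1/n₂), upper limit = RR × exp(1.96 × SE),

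with a events in n₁ women on carbetocin RTS and b events in n₂ women on oxytocin. For 291 v 291, SE = √(2 × (1/291 − 1/14,550)) = 0.0821, and the upper limit is exp(0.1609) = 1.175.

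The article gives no withdrawal rate. As an assumption, 5 or 10 women with severe PPH are removed from one arm only, from both numerator and denominator:

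| Women removed | RR | Upper limit |
|---|---|---|
| none | 1.000 | 1.175 |
| 5, carbetocin RTS | 0.983 | 1.156 |
| 10, carbetocin RTS | 0.966 | 1.137 |
| 5, oxytocin | 1.017 | 1.195 |
| 10, oxytocin | 1.035 | 1.217 |

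All limits stay below 1.23.

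**Near the margin.** With 291 oxytocin events, 305 carbetocin RTS events still pass (limit 1.229). At 308 v 291 the limit is 1.240, which fails. Removing 5 carbetocin RTS events gives 303 v 291 and a limit of 1.221, which passes. In that narrow zone the verdict depends on which rule is followed.

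**Power.** If withdrawal cost a further 0.5 % to 3 % of women on top of the 3 % (assumption), evaluable numbers would be 28,950 to 28,200. Power would be 79.8 % to 78.8 %, against 80.0 % at 29,100.

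**The case against.** The two statements can be reconciled. The rule under Inclusion/exclusion criteria concerns data retention and does not name an analysis set. Data collected before withdrawal have a place in the full ITT set and, for treated women, in the safety population. If withdrawing consent under Analysis populations means withdrawing consent to the use of one's data, nothing conflicts. That is a fair reading, but the article does not state it, and the retained data would otherwise be missing from the set that decides.

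A reader might infer that the article contains rival definitions of modified ITT, with different denominators for the same claim. It does not. Only Analysis populations defines the set. The sample-size text is a planning allowance that also covers women lost from per-protocol alone: "due to exclusion of women with a caesarean section or abortion after randomization, and those who are not protocol-compliant (excluded only in the per-protocol analysis". For the same reason, part of the 3 % is spare for modified ITT, so the power figures above overstate the cost there.

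A birth classed as abortion is already ineligible, and per-protocol requires compliance with the entry criteria. Only its modified ITT status is open, which the full protocol may settle.

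Blinding prevents withdrawal from depending on known allocation. It does not prevent dependence on bleeding or adverse events, so that part of the concern stands.

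**Conclusion.** The point holds as a conflict of wording in a decisive analysis set. Taken literally, the modified ITT definition removes observed primary outcomes of women who never asked for removal, and it does so on a post-treatment event.

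A reader might conclude that this breaks the randomised comparison or endangers the power. The documents do not support that. No withdrawal rate is given, and the bias could run in either direction. With 291 events per arm and a true relative risk of 1.00, losing 10 events from one arm still leaves the upper limit at 1.137 or 1.217. The conclusion could change only for a result already close to 1.23, such as 308 v 291 events. These figures rest on 2 % severe PPH, 14,550 women per arm, an interval unadjusted for country, and an assumed one-sided loss of 5 to 10 events.

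The mismatch on abortion is secondary: a point to align, not a competing population definition.

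**What to change.** Amend the modified ITT definition under Analysis populations to exclude women with a caesarean section after randomisation and, for withdrawal, only women who ask that their data not be used. State that women whose primary endpoint was measured before they withdrew otherwise stay in. This follows the retention rule the protocol already has.

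Also state whether a birth classed as abortion after randomisation is excluded from modified ITT, so that the definition and the sample-size allowance agree.

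The cost is a sentence or two, with no new data and slightly more women retained. Recruitment has started, so the wording should be settled before unblinding, when results cannot influence it.
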